### Design

2.1

This study is a single-center prospective observational study. It is intended to employ a suite of physiological and medical instruments in conjunction with internationally recognized standardized physiological and psychological questionnaires to dynamically monitor the physiological and psychological acclimatization of medical professionals from Peking Union Medical College Hospital. The monitoring will be conducted at seven key time points: prior to departure from Beijing, within 1–7 days post-arrival in Tibet during the acute phase of plateau hypoxia stress, during 2-week, 3-month, 6-month, and 12-month stays in Tibet during the chronic phase of plateau hypoxia stress, and upon return to Beijing.

The physiological parameters to be assessed include blood pressure, heart rate, fingertip venous oxygen saturation, hemoglobin concentration, hematocrit, physical phenotype, electrocardiogram conduction, cardiovascular function, and pulmonary function. Concurrently, questionnaires will be administered to assess acute mountain sickness, sleep quality, and emotional state. Blood, fecal, oral, and urine samples will be collected for further analysis, encompassing blood biochemical measurements, blood leukocyte whole gene expression profiling, blood proteomics, blood metabolomics, fecal metagenomics, fecal metabolomics, oral microbiota metagenomics high-throughput sequencing, and urine microprotein detection. Additionally, fundus examination and a six-minute walk test will be conducted.

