#### Basic physiological parameters

2.3.1

With respect to physiological parameters, the blood pressure, heart rate, and fingertip arterial oxygen saturation of the medical personnel are monitored utilizing an electronic sphygmomanometer and a pulse oximeter, respectively. A body composition analyzer is employed to quantify body weight, body mass index (BMI), body age, visceral fat index, basal metabolic rate, and the percentage of fat and muscle in various body segments.

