#### Cardiopulmonary function and fundoscopic examination

2.3.2

Regarding cardiopulmonary function assessment, a 12-lead electrocardiogram (ECG) device is utilized to examine the ECG conduction attributes, encompassing resting ECG and heart rate variability analysis. A cardiac function monitor is employed to assess cardiovascular function, including metrics such as heart rate, blood pressure, cardiac pumping and systolic functions, left heart workload, and peripheral vascular resistance. Pulmonary function testing is conducted to evaluate changes in maximum vital capacity, forced expiratory volume in one second (FEV1), and FEV1-to-forced vital capacity ratio (FEV1/FVC). Moreover, a 6-min walk test is administered to assess exercise endurance and cardiopulmonary function (13). Additionally, a fundoscopic examination is performed to inspect the vascular morphology of the fundus, to determine the presence of edema, and to ascertain any signs of hemorrhage (14).

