#### Subjective assessments

2.3.3

Subjective assessments are conducted using the Lake Louise Acute Mountain Sickness Symptom Rating Scale to gauge the incidence of acute mountain sickness among the medical support staff in Tibet (15). The Adult Self-rating Health Scale is employed to evaluate scores for anxiety, depression, hostility, and somatization symptoms (16). The Pittsburgh Sleep Quality Index is utilized to assess alterations in subjective sleep quality (17). The Depression-Anxiety-Stress Scale is used to gauge the emotional state of the Tibetan medical professionals (18). Additionally, a questionnaire survey is conducted to evaluate the perception of oxygenation, oxygen comfort, thermal sensation, and thermal comfort under various experimental conditions (19).

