#### Biological sample collection

2.3.4

For the procurement of blood, stool, urine, and oral samples, cubital vein blood is drawn for the analysis of hemoglobin concentration (20), hematocrit (HCT), and the calculation of the ratio of blood oxygen saturation to HCT. Further biochemical analyses included glucose (GLU), lipase (LIP), serum testosterone (T), ferritin (FERR), progesterone, vascular endothelial growth factor (VEGF), myoglobin (MYO), human interleukin-1β (IL-1β), total bilirubin (BILT), and alpha-amylase pancreatic (AMY-P) levels (21), as well as omics analyses. Fecal and oral samples are collected for subsequent metagenomic and fecal metabolomics high-throughput sequencing. Urine samples are analyzed for urinary α1-microglobulin (α1-MG), urinary β2-microglobulin (β2-MG), and microalbumin (mAlb) (22). Oral microbial community samples are obtained from participants prior to any eating, drinking, or tooth brushing upon waking in the morning. Sterile cotton swabs are used to thoroughly swab and rotate on the buccal mucosa, tongue base, and saliva, with the swab tips then placed in cryopreservation tubes and stored at −80°C pending metagenomic sequencing (23).

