### Statistical analysis of detection indicators

2.5

SPSS V.26.0 will be used as the statistical software. Quantitative data with a normal distribution will be presented as means with standard deviations and will be compared between groups with the use of Student’s t-test or the rank-sum test. Quantitative data that do not follow a normal distribution or homogeneity of variance will be presented as median and IQR, and comparisons between groups will be performed by the Mann–Whitney U test. Enumeration data will be presented as ratios and percentages, and χ^2^ tests will be used for comparison. Two-tailed *p* < 0.05 is considered statistically significant.

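### Section 2.5 sets one flat p<0.05 for about 50 indicators over seven visits, with no lead indicator and no exploratory label

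*Protocol article*

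**What the plan says.** Section 2.5 names Student's t-test, the rank-sum or Mann–Whitney U test and the chi-square test. All are framed as comparisons between groups; for non-normal data, for example, "comparisons between groups will be performed by the Mann–Whitney U test". The section closes with one threshold for everything it covers: a two-tailed p below "0.05 is considered statistically significant". It ranks no indicator and gives no number of contrasts.

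The indicators are listed in sections 2.3.1 to 2.3.4. Examples are:
- vital signs: "the blood pressure, heart rate, and fingertip arterial oxygen saturation of the medical personnel are monitored"
- body composition: "body weight, body mass index (BMI), body age, visceral fat index, basal metabolic rate, and the percentage of fat and muscle in various body segments"
- cardiac function: "heart rate, blood pressure, cardiac pumping and systolic functions, left heart workload, and peripheral vascular resistance"
- questionnaires, one of which is used to "evaluate scores for anxiety, depression, hostility, and somatization symptoms"
- blood tests: "Further biochemical analyses included glucose (GLU), lipase (LIP), serum testosterone (T), ferritin (FERR), progesterone, vascular endothelial growth factor (VEGF" and others

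On timing, section 2.1 says "The monitoring will be conducted at seven key time points". The omics analyses are described separately in section 2.4 and are not counted here. Section 3 and the Discussion acknowledge the small sample (17 people) but say nothing about the number of tests.

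**The concern.** A threshold of 0.05 limits the error of one test. Here it is the stated rule for a long list of indicators, each measured repeatedly, and nothing marks one result as the main one. A reader of the eventual report could not tell a contrast chosen in advance from one picked out of hundreds because its p-value was small.

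With 17 participants there is little inside the study to separate a chance shift from a real one. The Discussion hopes to identify targets for prevention and treatment of altitude illness and to inform work plans for deployed staff. An unqualified claim of significance on a chance finding would therefore carry weight that it has not earned.

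**Working it through.** There is no derived figure to reproduce. The 0.05 is declared by convention, and the sample of 17 comes with no effect size, standard deviation or power.

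**Step 1: count the indicators (sections 2.3.1 to 2.3.4, omics excluded).**

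| Group | Count |
|---|---|
| Vital signs (blood pressure counted once) | 3 |
| Body composition (segments not split) | 7 |
| Resting ECG, heart rate variability, four cardiac measures | 6 |
| Lung function | 3 |
| Six-minute walk | 1 |
| Fundus | 3 |
| Questionnaires: Lake Louise 1, self-rating health 4, sleep 1, depression-anxiety-stress 1, oxygen and thermal 4 | 11 |
| Blood: hemoglobin, hematocrit, saturation/hematocrit ratio, 10 analytes | 13 |
| Urine | 3 |
| **Total** | **50** |

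This is a low-end count. Blood pressure as two values (+1) and the depression-anxiety-stress scale as three (+2) make it 53.

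**Step 2: contrasts per indicator.** The article does not fix this, so three schemes are shown. Seven visits give 7 − 1 = 6 contrasts against pre-departure, 7 two-group comparisons (one per visit), or 7 × 6 / 2 = 21 visit pairs.

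**Step 3: expected false positives if nothing changes.** The formula is 0.05 × indicators × contrasts. It holds whatever the correlation between indicators, provided each test truly has a 5% error rate.

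| Scheme | Tests (50) | Expected (50) | Expected (53) |
|---|---|---|---|
| One contrast | 50 | 2.5 | 2.65 |
| Six against pre-departure | 300 | 15 | 15.9 |
| One two-group comparison per visit | 350 | 17.5 | 18.55 |
| All 21 visit pairs | 1,050 | 52.5 | 55.65 |

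For one contrast across 50 independent indicators, the chance of at least one false positive is 1 − 0.95^50 = 92%.

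**Step 4: correlation between indicators.** In 2,000 simulated null studies (17 people, 7 visits, 50 indicators, assumed correlation 0.3 between indicators, paired t-tests against the first visit), the mean was 14.8 false positives. The 5th to 95th percentile range was 5 to 32, and every run had at least one.

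**Step 5: a single indicator.** In null simulations with 17 people and paired t-tests, the chance of at least one false positive was 20–21% over six contrasts and 46–47% over 21 pairs.

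**Step 6: if some indicators truly change.** The count scales with the share that does not. If half are unchanged, 15 becomes 7.5, 17.5 becomes 8.75 and 52.5 becomes 26.25.

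**Step 7: if the named independent-sample tests are used across visits.** An unpaired test on the same people at two visits is conservative when a person's visits are positively correlated. The article gives no such correlation, so a range is assumed. The error rates are simulated null rates for the unpaired t-test with n = 17.

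| Assumed within-person correlation | Error per test | Six contrasts (300 tests) | All pairs (1,050 tests) |
|---|---|---|---|
| 0 | 0.048 | 14.4 | 50.4 |
| 0.3 | 0.022 | 6.6 | 23.1 |
| 0.5 | 0.008 | 2.4 | 8.4 |
| 0.7 | 0.001 | 0.3 | 1.05 |

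The per-visit two-group figure of 17.5 is not affected, because those groups contain different people.

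**The case against.** The strongest reply has four parts.

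**The article is condensed.** A statistical analysis plan may exist and could hold a hierarchy or an adjustment. A stated 0.05 does not exclude adjusted p-values, and the study is observational with descriptive aims. This stands in part: it cannot be said that no adjustment will be made. But section 2.5 does state a rule and attaches the words of significance to it without qualification. That rule is what readers will hold the results to.

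**The scheme of tests is not given.** A reader might infer that every indicator will be tested at every visit. Section 2.5 speaks only of comparisons between groups and sets out no visit-by-visit scheme. This stands, and it is why the size is given per scheme.

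**The counts depend on which tests are run and on a full null.** Both points stand. The visit-contrast figures assume paired or otherwise validly sized tests, and the unpaired tests named would give fewer false positives across visits. That mismatch between tests and design is a separate defect, and correcting it brings the full counts back. The Introduction also describes established changes at altitude, so a state in which nothing changes is not what the authors expect.

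**The omics work does not depend on the threshold.** A reader might infer that indicators passing p<0.05 are the ones carried into the omics integration. Section 2.1 describes no such gate. It relates omics results to changes in the biomarkers and compares groups formed by indicator values. That inference has no support in the text and is not part of this point.

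**Conclusion.** The point holds. One flat two-tailed 0.05 is the stated rule for about 50 non-omics indicators at seven visits, with no lead indicator and no exploratory label.

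With validly sized tests and no true change, about 2.5 false positives are expected per contrast. That is about 15 for six contrasts against pre-departure and about 17.5 for one two-group comparison per visit.

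It is tempting to say that dozens of chance findings are to be expected. The article does not support that as a general statement. A count over 50 needs all 21 visit pairs and a full null, and the article specifies neither.

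The figures rest on a low-end count of 50 indicators, on an assumed number of contrasts, and on tests with a true 5% error rate. They shrink in proportion to the share of indicators that truly change.

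This should be corrected, but it does not undermine the data collection.

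**What to change.** In section 2.5:

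1. Name one physiological and one psychological lead indicator, each with one visit contrast, tested at 0.05. The investigators should choose them before looking at the data. The chance of at least one false positive across the two is then at most 0.05 + 0.05 = 10%.
2. For every other indicator, test the overall visit effect with a repeated-measures method. Control the false discovery rate at 5% across indicators (Benjamini-Hochberg).
3. Examine visit contrasts only for indicators that pass, with Holm adjustment within the indicator.
4. Label everything outside the two lead contrasts as exploratory.

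This remains workable with 17 people. Holm's strictest step is 0.05 / 6 = 0.0083 for six contrasts, or 0.05 / 21 = 0.0024 for all pairs. The smallest two-sided exact p from a paired signed-rank test is 2 / 2^17 = 0.000015. A Bonferroni correction over all tests would be much harsher: 0.05 / 300 = 0.00017, or 0.05 / 1,050 = 0.000048.

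The cost is a few sentences and some extra analysis, with no new data. The downside is that fewer secondary indicators will be called significant.

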### Trial management

2.6

The selection and sampling of study subjects will be carried out in strict accordance with the study design requirements. We will implement a document management approach to ensure data authenticity, completeness, reliability, and comparability. The analysis of the experimental data will be scientific, the research report will be authentic and rigorously written, and the research data will be properly archived and stored in accordance with the research storage guidelines.

### Patients and public involvement

2.7

Patients and/or the public are not involved in the design, or conduct, or reporting, or dissemination plans of this trial.

### Confidentiality

2.8

In the course of this investigation, personal and medical information pertaining to the study participants may be gathered or processed, encompassing, but not limited to, the following details: full name, gender, date of birth, residential address, contact telephone number, and diagnostic outcomes of the medical professionals providing support in Tibet. The personal data of the Tibet-supporting physicians will be utilized exclusively for the objectives delineated within the study’s protocol. Medical information obtained by the Tibet-supporting physicians affiliated with the institution will be maintained with strict confidentiality. Publication of study findings in academic periodicals will be conducted in a manner that precludes the disclosure of any personally identifiable information that could trace back to the physicians supporting Tibet. The principal investigator assumes responsibility for the secure storage and appropriate utilization of all personal data pertaining to the Tibet-supporting medical professionals involved in the study. The ethics committee or the clinical research regulatory authority may gain access to the personal data of these professionals as required. The research team will exert every feasible measure to safeguard the privacy of the personal medical data of the supporting physicians, in full compliance with legal provisions.

### Data management

2.9

The sample collection mentioned in section 2.3 will be conducted by experienced doctors, and during the period in Tibet, the same group of doctors will complete the task to ensure the avoidance of potential biases. The subjective questionnaires will be distributed online to participants in the form of electronic questionnaires, which participants will complete on their own mobile phones. The collected biological samples will be stored in a dedicated biobank refrigerator at Peking Union Medical College Hospital, and the other information will be saved on an in-house computer at Peking Union Medical College Hospital, which is accessible only to specific members of this research team, fully ensuring the security and privacy of the data.

## Strengths and limitations of this study

3

(1) The study is anticipated to enhance our comprehension of the physiological underpinnings and psychological manifestations of hypoxic acclimatization.(2) By concurrently monitoring physiological and psychological indicators at the same time points, this study aims to elucidate the potential correlation between these two domains.(3) The study is expected to contribute to the identification of etiological factors and risk profiles associated with altitude-related illnesses.(4) The sample size is anticipated to consist of 17 volunteers, which may pose challenges to statistical robustness and generalizability.

## Ethics and dissemination

4

The Peking Union Medical College Hospital’s Research Ethics Committee has provided ethical clearance for this study, designated with the approval code 2022-I2M-1-003. The study protocol has been sanctioned and registered with the ClinicalTrials.gov, bearing the registration number NCT06557928. The results of this trial will be disseminated in an open-access format, with the intention of sharing the findings among medical professionals.

## Discussion

5

This study aims to conduct an exhaustive examination of the impact of high-altitude hypoxia acclimatization on human physiological and psychological metrics, as well as to investigate the potential interconnection between these two domains. The research endeavors to delineate the regulatory pathways underlying the physiological and psychological phenotypes elicited by hypoxia in the Tibetan plateau, thereby providing scientific evidence and identifying potential targets for the medical prophylaxis and treatment of altitude-induced illness. Furthermore, the findings are intended to furnish medical expertise for the development of work plans for personnel deployed to support medical services in Tibet.

The cohort of this investigation comprises medical practitioners from the Peking Union Medical College Hospital who are engaged in providing healthcare services in Tibet. The hospital’s robust management infrastructure facilitates the efficient procurement of data over the course of the two-year study period. Nonetheless, the limited sample size inherent to this study may present challenges in the interpretation of omics findings and the conduct of statistical analyses. Should circumstances permit, subsequent experimental iterations may augment the sample size to enhance the robustness and generalizability of the results.
